## Data analyses

### Statistical Power Calculation

Since the trial proceeded in phases, the initial data collected in year 1 was used to determine the overall sample size needed for the trial. Based on the variances observed in the primary endpoints in the year 1 cohorts, a sample size of *N* = 120 in total was needed to provide at least 80% power (two-sided, α = 0.05) to detect between-group differences of 20 mg/dl in fasting glucose and 1.0% in HbA1c.

### Statistical Analyses

All data will be analyzed using two-sided statistical tests and a Type I error rate of α = 0.05. The intention-to-treat method will be used for the primary analyses but will be compared to outcomes from actual-treatment-received analyses (i.e., per protocol analyses). Categorical data will be compared between the two groups using chi-square or Fisher's exact tests. Continuous data will be compared using linear mixed models or non-parametric tests (as appropriate), with potential adjustments for changes in medication dosages and potential covariates such as baseline values, age, biological sex, and cohort number. Likelihood functions will be examined to determine the appropriateness of covariates and to avoid overfitting the data. Multivariable linear and logistic regression will be used to identify predictors for improved health outcomes. Lastly, subgroup analyses may be performed by sex, age, co-morbidity, length of diagnosis, and severity to evaluate heterogeneity in treatment responses.

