Despite the promise of such lifestyle interventions, implementing them in indigenous populations such as the RMI presents unique challenges. Research has shown that such interventions are more effective when they are culturally-sensitive and delivered to communities, rather than to individuals or families (66). In the late 1990's, Canvasback Missions, Inc., recognized the need for such interventions in the RMI and conducted two lifestyle intervention programs with excellent results, using a modified version of the NEWSTART® wellness program operated by the Guam Seventh-day Adventist Clinic (67). The program emphasizes a whole-food, plant-rich diet with moderate exercise and is used to treat T2D, obesity, and other chronic diseases. Although no studies have been published on the intervention, Guam physicians have found it effective and continue to refer their patients to wellness centers (68).

Building on the success of these lifestyle intervention programs in Guam and the RMI, we designed and conducted the first randomized controlled trial to rigorously evaluate whether a comprehensive, culturally-sensitive, lifestyle intervention program can treat T2D in the RMI. The goal of the study was to determine the effectiveness of an intensive lifestyle intervention consisting of a mostly plant-based diet and regular moderate exercise in Marshall Islanders with T2D. The present study was also the first randomized clinical trial ever conducted in the RMI and the first lifestyle intervention trial ever conducted in Micronesia. The primary aim was to determine whether the lifestyle intervention can improve glycemic control. The primary endpoints included fasting glucose, fasting insulin, HbA1c, insulin resistance as measured by the Homeostatic Model Assessment of Insulin Resistance (HOMA-IR), and usage of diabetes medications. The secondary aim was to determine whether the lifestyle intervention could improve cardiovascular risk factors, including lipids, blood pressure, heart rate, high-sensitivity C-reactive protein (hs-CRP), body weight, body mass index (BMI), and waist circumference. We hypothesized that study participants would be able to make sufficient lifestyle changes—including by modifying their diet and increasing their physical activity—to achieve clinically meaningful improvements in glycemic control and cardiovascular risk factors, relative to the control group.

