#### Medications

To monitor changes in glucose levels in the intervention group and adjust medication dosages accordingly, a glucometer was used during the first 2 weeks and fasting labs at weeks 2, 6, and 12 were relied on thereafter. Medication dosages were adjusted by participants' primary care physicians and/or the DWC clinicians. Medications and their dosages were recorded at each assessment. Changes in the average number of medications and in the percentage of participants taking one or more medications will be compared across groups for both all medications and diabetes-specific medications.

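### The only test stated for the percentage on medication takes no account of recorded baseline status; it is valid, but can lose substantial power for a measure defined as a change

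*Protocol article*

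**What the plan says.** The Introduction of the protocol article lists the primary endpoints, ending with "insulin resistance as measured by the Homeostatic Model Assessment of Insulin Resistance (HOMA-IR), and usage of diabetes medications". It gives no metric for the last of these.

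The Medications section supplies two: "Changes in the average number of medications and in the percentage of participants taking one or more medications will be compared across groups". Both are to be examined for all medications and for diabetes medications alone. The same section says: "Medications and their dosages were recorded at each assessment". Under Assessments, that means weeks 0, 2, 6, 12 and 24.

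Statistical Analyses sets the general rule, "All data will be analyzed using two-sided statistical tests and a Type I error rate of α = 0.05", and then one line for this type of data: "Categorical data will be compared between the two groups using chi-square or Fisher's exact tests". Linear mixed models and possible adjustment for baseline values are named for continuous data. Logistic regression appears only as a way to find predictors of improvement, not to compare the arms.

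The Statistical Power Calculation covers glucose and HbA1c only.

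**The concern.** The binary medication measure is framed as a change from baseline, but the method stated for binary data has no place for baseline. If participants mostly stay on, or mostly stay off, medication, much of the spread in week-24 status is already present at week 0. A test that does not use week 0 counts that spread as noise.

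The Discussion expects many participants to cut back on diabetes drugs. At stake is whether a real reduction in the percentage on medication would be detected. The eligibility criteria exclude anyone whose diabetes-related dosage changed in the previous 3 months, which makes stable status plausible at entry.

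**Working it through.** **The plan's own figure.** N = 120 is stated for 80% power "to detect between-group differences of 20 mg/dl in fasting glucose and 1.0% in HbA1c". No SD is given, so it cannot be checked independently. With 60 per arm, SD = d × √[60 / (2 × (1.96 + 0.842)²)] = 1.955 d. The implied SDs are 39.1 mg/dl and 1.955% HbA1c. This says nothing about medication use, so 60 per arm is taken below only as a sample size.

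**Inputs.** From the article: two-sided α = 0.05; 60 per arm planned; 79 versus 90 when the cohort counts are added (13+21+9+14+22 and 14+20+22+13+21). Assumed, because the article gives no values: fraction p on a drug at baseline, fraction s of users who stop, fraction t of non-users who start.

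**Central case:** p = 0.75; s = 0.20 (intervention) and 0.02 (control); t = 0.05 in both arms.

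1. Percentage on a drug at follow-up, f = p(1−s) + (1−p)t:
   - Intervention: 0.75×0.80 + 0.25×0.05 = 0.6125
   - Control: 0.75×0.98 + 0.25×0.05 = 0.7475
   - Difference: 0.135

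2. Test ignoring baseline. The pooled fraction is 0.68.
   - Null SE = √(2×0.68×0.32/60) = 0.0852
   - SE under the alternative = √[(0.6125×0.3875 + 0.7475×0.2525)/60] = 0.0843
   - Power ≈ Φ[(0.135 − 1.96×0.0852)/0.0843] = Φ(−0.38) ≈ 35%

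3. Test conditioning on baseline. The variance per participant is p·s(1−s) + (1−p)·t(1−t).
   - Intervention: 0.75×0.16 + 0.25×0.0475 = 0.1319
   - Control: 0.75×0.0196 + 0.25×0.0475 = 0.0266
   - SE = √[(0.1319 + 0.0266)/60] = 0.0514
   - Power ≈ Φ(0.135/0.0514 − 1.96) = Φ(0.67) ≈ 75%

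Simulation (20,000 or more trials per setting) agrees: 36% to 37% for chi-square on final status, 76% for the baseline-stratified Mantel-Haenszel test, and 75% for raw change (−1/0/+1).

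**Other assumed rates** (simulated power):

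| Per arm | Baseline on drug | Stop, int./control | Start, int./control | Chi-square, final status | Raw change | Stratified |
|---|---|---|---|---|---|---|
| 60/60 | 75% | 15%/2% | 5%/5% | 22% | 54% | 55% |
| 60/60 | 75% | 25%/2% | 5%/5% | 52% | 89% | 90% |
| 79/90 | 75% | 20%/2% | 5%/5% | 46% | 87% | 90% |
| 60/60 | 90% | 20%/2% | 5%/5% | 62% | 89% | 89% |
| 60/60 | 75% | 20%/2% | 30%/70% | 91% | 85% | 96% |
| 60/60 | 70% | 40%/20% | 30%/50% | 62% | 50% | 65% |

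Over a wider grid (baseline 50% to 100%, various stop and start rates), the gain over final-status chi-square was:
- stratified test: about 0 to 53 points at 60/60, and 0 to 59 at 79/90;
- raw change: −13 to +51 points at 60/60, and −14 to +59 at 79/90.

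With everyone on medication at baseline there is a single stratum, so the stratified test and chi-square coincide and the gain is about 0.

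**Type I error.** With the same stop and start rates in both arms, final-status chi-square rejects in 4.6% to 5.5% of trials. The stratified test stays at or below about 5%, and is conservative when few participants change status.

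**The case against.** **The size rests on assumptions.** This is the strongest objection, and it stands. Non-users had to qualify on HbA1c of at least 8.0%, and usual care includes starting drugs appropriate to HbA1c, so a 5% start rate in controls may be far too low. If 50% of control non-users start (5% in the intervention arm), the central case gives chi-square 89% against 98% for raw change. Year-2 cohorts (31+27+43 = 101 of 169) came mainly from the diabetes clinic, so baseline use may be high and the loss small. A fixed loss cannot be claimed.

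**A different null.** A reader might infer that the chi-square test answers another question. Under randomisation both arms have the same expected baseline percentage, so equal follow-up percentages and equal changes are the same null in expectation. They part only through chance imbalance.

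**Power against a planned alternative.** A reader might also take the loss as measured against the trial's own target. The article states no target for medication use.

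**An untested endpoint.** This does not follow either. Chi-square on participant-level categories (stopped, started, unchanged) would be legitimate and is not excluded. In the central case, chi-square on stopped yes/no has about 84% power. But it ignores starters: at 79/90, with 50% on a drug at baseline, stopping 15% versus 2% and starting 0% versus 10%, it has 60% against 92% for the stratified test. The article does not say such coding is meant.

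**Scope.** The average number of medications falls under the rule for continuous data, where baseline adjustment is possible. Only diabetes medication use is primary.

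**Detail left to an analysis plan.** Time point and coding can properly be left there. The article is not silent on method, however: it states a test for this data type, and on its ordinary reading that test is a poor match for a change measure.

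**Conclusion.** The point holds as a matter of efficiency, not validity. For a measure described as a change from baseline, and forming part of a primary endpoint, the only stated test makes no use of baseline status recorded for that purpose. Power is about 37% against about 76% under the central assumptions. The loss runs from about 0 to 40 points or more across plausible rates, none of which the article documents.

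The recommendation is firmer than the size. In every scenario tabulated the stratified test beat final-status chi-square, and over the wider grid it did about as well or better. Raw change did not: it fell behind chi-square where many participants changed status.

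**What to change.** For any diabetes drug and for any drug, replace the unadjusted chi-square or Fisher test with an analysis that conditions on baseline status. Options are logistic regression adjusted for baseline status, a Mantel-Haenszel test stratified by it, or a repeated-measures binary model with baseline as a covariate. Report the between-arm difference in percentage on medication with a 95% CI. Under randomisation this difference also estimates the difference in change.

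Do not use a raw change score. Keep chi-square and Fisher's exact test for categorical items measured at a single time.

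The cost is a sentence in the analysis plan, slightly more modelling, and a fallback for sparse cells such as an exact stratified test. No new data are needed. The analyses are still described in the future tense, so the change can be made before they are run.

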The management of adverse events and data collection in a country with no prior research infrastructure presented the greatest challenges to the trial. The main challenge for adverse event management was adjusting medication dosages downwards to avoid hypoglycemic reactions in the intervention group. When participants were not in the clinic, they often had to return to their family physician to adjust their medication dosages, which meant long wait times and a fee. This was particularly problematic for participants on insulin, who had to be very carefully monitored so that insulin dosages could be reduced or stopped accordingly. Further, because medication dosing tended to increase for control subjects and decrease for intervention subjects, future reported outcomes will likely be biased toward the null hypothesis. We also faced problems with missing data due to participants not showing up for appointments, procedural failures by the laboratory, and the hospital being new to the extensive documentation requirements for clinical trials, in a country where clinical trials have never been performed before. It took several trips and digging through boxes of duplicate lab slips to fill in missing logbook entries. The positive outcome is that new policies and reporting procedures were established for any future lab work that may be required, and all lab work that was done is now backed up. To tackle the challenge of participant attendance at clinic visits, research staff attempted to reach every participant by phone, and in some cases, went to the participant's home or work to remind them of the importance of the blood draws and measures to complete the study. We have discovered that within the RMI, more effort is needed than in the U.S. to ensure that participants fully participate in the intervention.

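### The plan leaves the intention-to-treat comparison of glycaemic outcomes open to adjustment for on-trial medication dosage change, which is itself affected by treatment

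*Protocol article*

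**What the plan says.** All references are to the protocol article.

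- **Statistical Analyses, principle:** "The intention-to-treat method will be used for the primary analyses", to be compared with per-protocol results.
- **Statistical Analyses, model:** "Continuous data will be compared using linear mixed models or non-parametric tests (as appropriate"), and the same sentence continues "with potential adjustments for changes in medication dosages" and names baseline value, age, sex and cohort as further possible covariates. It applies to all continuous data and singles out no primary model. The next sentence decides which covariates are appropriate by examining likelihood functions.
- **Introduction:** the primary endpoints are fasting glucose, fasting insulin, HbA1c, HOMA-IR "and usage of diabetes medications".
- **Medications:** the purpose of the glucometer and the fasting labs is stated as "To monitor changes in glucose levels in the intervention group and adjust medication dosages accordingly". Medications and dosages were recorded at each assessment. As an outcome, "Changes in the average number of medications and in the percentage of participants taking one or more medications will be compared across groups".
- **Discussion:** the authors expected many participants to rely less on diabetes drugs. They report that outcomes will probably be biased toward the null "because medication dosing tended to increase for control subjects and decrease for intervention subjects".

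**The concern.** One sentence puts two kinds of variable side by side. Baseline value, age, sex and cohort are fixed before randomisation, and adjusting for them leaves the intention-to-treat comparison intact. Dosage change is not of that kind. It happens during follow-up, it is one of the things the intervention is meant to alter, and in the intervention arm it responds to glucose, which is itself a primary outcome.

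Putting such a variable in the model does two things. It removes the part of the arm difference that runs through medication. It also compares participants with the same dosage change, who will differ between arms in underlying severity because severity helped to determine the dosage change.

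The likelihood rule gives no protection. It rewards association with the outcome, and a variable titrated on glucose will often be associated with glucose and HbA1c whether or not it belongs in the model. The choice would also be made when the direction of dosing in each arm is already known. At stake is what the headline glycaemic effect means.

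**Working it through.** **Plan's own figure.** The article gives no number for this point. Its one design figure, N = 120, cannot be reproduced because no SD is printed, and the point does not depend on it.

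**Is dosage change a baseline covariate?** No, by the article's own account. It is recorded at follow-up visits, it follows glucose in the intervention arm (Medications), a reduction is an expected effect of the intervention, and its direction differed by arm (both Discussion).

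**What does the adjusted coefficient estimate?** Take a simple model. Every value in it is an assumption, since the article gives no dose-response, titration slope or dosing variance.

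- A is arm; U is unmeasured severity with SD 1; the effect with medication held fixed is -0.80.
- Response before medication: Y0 = U - 0.8A.
- Dosage change: M = kY0 + noise with SD s.
- Outcome: Y = Y0 - bM + error.

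Total (intention-to-treat) effect: -0.8(1 - bk).

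Coefficient of A with M in the model: the slope of U on M within arm is k/(k² + s²), and the arms differ in mean M by -0.8k. The coefficient is therefore -0.8 + 0.8k²/(k² + s²) = -0.8s²/(k² + s²).

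| k | b | s | Total effect | Adjusted for M |
|---|---|---|---|---|
| 0.3 | 0.4 | 0.5 | -0.8 × 0.88 = -0.70 | -0.8 × 0.25/0.34 = -0.59 |
| 0.5 | 0.4 | 0.5 | -0.8 × 0.80 = -0.64 | -0.8 × 0.25/0.50 = -0.40 |
| 0.8 | 0.4 | 0.5 | -0.8 × 0.68 = -0.54 | -0.8 × 0.25/0.89 = -0.22 |
| 0.5 | 0.4 | 1.0 | -0.8 × 0.80 = -0.64 | -0.8 × 1/1.25 = -0.64 |
| 0.5 | 0.8 | 1.0 | -0.8 × 0.60 = -0.48 | -0.8 × 1/1.25 = -0.64 |
| 0.1 | 0.4 | 0.5 | -0.8 × 0.96 = -0.77 | -0.8 × 0.25/0.26 = -0.77 |

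Simulation agrees with these values to within simulation error. The adjusted coefficient does not depend on b, the drug effect, while the total effect does. Agreement between the two is therefore a coincidence of parameter values. In no row does the adjusted coefficient reach -0.80.

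**Adding the baseline value**, which the plan also lists. If baseline correlates r with U, k² is replaced by k²(1 - r²). For k = 0.5, b = 0.4, s = 0.5 (total -0.64):

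- r = 0.7: -0.8 × 0.25/(0.25 × 0.51 + 0.25) = -0.53.
- r = 0.85: -0.8 × 0.25/(0.25 × 0.2775 + 0.25) = -0.63.

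Adding baseline brings the coefficient closer to the total in this case, but nothing guarantees that they meet.

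**A second structure on the HbA1c scale.** Dosage is titrated on an earlier HbA1c that shares a latent level with the final one. Assumed: SD 1.955, within-person correlation 0.7, fixed-dose effect -1.0%, dosing noise SD 0.7. The SD is the largest that N = 120 allows at 80% power: 1.0/(√(2/60) × 2.80) = 1.955. Simulated results:

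- Drug effect 0.25, titration slope 0.5: total -0.87, adjusted -0.53.
- Drug effect 0.5, slope 0.3: total -0.85, adjusted -0.71.
- Drug effect 1.0, slope 0.1: total -0.90, adjusted -0.95.
- No fixed-dose effect, drug effect 0.5, slope 0.3, dosage set 0.5 units lower in the intervention arm: total +0.26, adjusted +0.49.

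Again the coefficient generally equals neither target, and the sign of the gap to the total effect changes with the assumptions.

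**The case against.** The case for the plan has real force, and several stronger readings that a reader might infer do not stand.

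- *The primary results would be biased.* The article says only that the adjustment is potential, and it names no primary model that includes it. The analysis plan is not shown and may label the adjusted model supplementary. What can be said is that the published wording leaves this open.
- *The adjusted analysis answers no causal question.* The effect with medication held fixed is a legitimate question, and the Discussion's concern about opposing dose changes is a sensible motive for asking it. The weakness is the tool: ordinary covariate adjustment does not identify that effect when dosage responds to the outcome and both share unmeasured severity.
- *Adjustment always moves the estimate further from the truth.* It does not. With more dosing variation unrelated to glucose, the adjusted and total effects coincide (-0.64), or the adjusted value lies nearer to the fixed-medication effect than the total does (-0.64 against -0.48).
- *Every participant's dosage was driven by glucose response.* The Medications section says this of the intervention group. For controls, Usual Diabetes Care says only that the agents suited HbA1c levels.
- *The medication endpoint cannot see its main signal.* The named measures are the number of drugs and the percentage of participants on at least one. The article does not say these are the only measures, and it may leave dose coding to the analysis plan. Stopping a drug, which the Discussion mentions for insulin, changes the count.

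Dosage change and medication usage are also linked rather than identical, so the covariate is not literally a primary endpoint. After all this, the core remains: the document permits a treatment-affected covariate in the comparison it calls intention-to-treat, and does not restrict where that adjustment may be used.

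**Conclusion.** The point holds as a flaw in a stated analysis choice. If dosage change is included, the arm coefficient in general estimates neither the intention-to-treat effect that the plan makes primary nor, without strong further assumptions, the effect with medication held fixed. This follows from the order of events and from the article's own account of dosing, and it does not rest on the simulations.

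The size and direction cannot be determined from the documents. In the illustrations the gap between the adjusted and total effects runs from zero to about 0.3 SD (-0.54 against -0.22) and changes sign. These figures show what could happen and are not estimates for this trial. The sample size is unaffected.

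**What to change.** 1. Remove dosage change from the covariates allowed in the primary intention-to-treat models. Limit those models to variables measured before randomisation: baseline value, age, sex, cohort and, if wanted, baseline medication. State that the likelihood check applies only within that set.
2. Report medication change as an outcome alongside HbA1c and glucose, so that a reader can see how far opposing dose changes may have masked a glycaemic difference.
3. If a dose-adjusted or fixed-medication analysis is wanted, label it supplementary. State its question and assumptions, and use a method suited to confounding that treatment itself affects, such as a marginal structural model or g-estimation.

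The cost is a change of wording; the dosages for item 2 are already recorded. The downside is small: the primary HbA1c and glucose effects may look smaller where controls were titrated up and intervention participants down. The article describes the analyses in the future tense, with results still to be published, so the change can still be made.

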#### Cohorts

Participants were enrolled in five overlapping cohorts, with each cohort including both a control and intervention group (described below). Within each cohort, participants were randomized to one of the two groups in approximately equal numbers. The cohorts were spread over a two-year period, with Cohorts 1 and 2 finishing in year 1 and Cohorts 3–5 finishing in year 2. The cohorts 1–5 consisted of 27 (13 in the intervention group vs. 14 controls), 41 (21 vs. 20), 31 (9 vs. 22), 27 (14 vs. 13), and 43 (22 vs. 21) participants, respectively. The control arm received the usual standard of diabetes care, while the intervention arm received a lifestyle intervention. Unfortunately, not all participants in the control group in year 1 sought and received the usual standard of care for diabetes treatment as instructed, so starting in year 2, participants were primarily recruited from the MOH Diabetes Clinic, in order to ensure that the control group was compliant with the standard of care. Furthermore, to improve the delivery of the intervention, Cohorts 3–5 received an enhanced version of the lifestyle intervention. The enhanced version was identical to the standard version of the intervention, with the exception of more patient education and contact during weeks 4 and 6 of the study. The nature of the dietary and exercise intervention itself was not changed and did not vary across cohorts.

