The initial 12-week program was structured as follows. During the first 2-week intensive phase, participants in all cohorts attended 5–6 h/day of group classes on Mondays–Thursdays (4 days/week) at the DWC, totaling 36 h of health education over the first two weeks. Figure 1 displays the schedule for the intensive phase. On clinic days, group sessions included 1 h/day of exercise, and participants were fed 3 meals/day made by the DWC Kitchen, according to the menus shown in Table 2. Participants ate breakfast at the DWC and took lunch boxes with them to eat at work or at home. The participants then returned to the DWC for a 5-h session from 3:00 to 8:00 p.m., where they helped prepare the meals and then ate dinner. Participants prepared the main dish, and the kitchen staff made the side dishes (e.g., green salad). During weeks 3–6, participants who received the standard version of the intervention (Cohorts 1–2) spent 4–5 h twice per week (Tuesdays and Thursdays) in group sessions, including 60 min/day of structured exercise, a 10–20-min walk after each meal, and also consumed an evening meal provided by the DWC Wellness Kitchen (see menus in Table 3). For those receiving the enhanced version of the intervention (Cohorts 3–5), weeks 4 and 6 of the standard intervention were replaced with weeks 1 and 2 to increase the intensity of instruction, as shown in Table 1. During weeks 7–12 of the program, participants in all cohorts participated in a 4–5 h once per week session with structured exercise and group classes and were provided an evening meal. Finally, during the last 12 weeks of the trial (weeks 13–24), no instruction or counseling was provided, and participants came to the center weekly to turn in their pedometer readings.

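### Cohort, within which patients were randomised (9 vs 22 in cohort 3), and the baseline value should be fixed model terms, not optional covariates judged by likelihood

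*Protocol article*

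**What the plan says.** The Cohorts section of the protocol article makes cohort the unit within which allocation took place: "Within each cohort, participants were randomized to one of the two groups in approximately equal numbers". It then gives the counts. Cohort 1 is 13 intervention vs 14 control, and cohorts 2 to 5 are "41 (21 vs. 20), 31 (9 vs. 22), 27 (14 vs. 13), and 43 (22 vs. 21) participants".

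The same section and the Discussion describe changes between year 1 (cohorts 1 and 2) and year 2 (cohorts 3 to 5): recruitment mainly from the diabetes clinic, better uptake of standard care among controls, an enhanced programme, and materials in Marshallese.

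Statistical Analyses says that continuous outcomes will be compared with linear mixed models or non-parametric tests. Possible adjustments include "potential covariates such as baseline values, age, biological sex, and cohort number". The selection rule is: "Likelihood functions will be examined to determine the appropriateness of covariates and to avoid overfitting the data". Categorical data go to chi-square or Fisher's exact tests, with no mention of cohort. Medications names one such outcome, the percentage of participants taking one or more medications, for diabetes drugs and for all drugs. The Introduction lists diabetes medication use among the primary endpoints.

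**The concern.** An analysis should respect the groups within which patients were randomised. That matters more when the allocation ratio differs between those groups, because arm is then associated with cohort and an unadjusted comparison mixes the treatment effect with cohort differences. Here one cohort is far from 1:1 and the other four are almost exactly 1:1.

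The plan does not promise to adjust. It makes cohort, and even the baseline value of the outcome, candidates to be judged on the data. The trial was not blinded. The last cohort began in July 2008, and Recruitment says the data were not analysed until the time of writing. The primary model would therefore be settled with the outcome data in hand. For the medication percentage, the named tests cannot use cohort at all.

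The article states a rule here, so this is more than silence. A separate analysis plan that fixed these terms would have to override that rule.

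**Working it through.** **Counts.** Intervention: 13 + 21 + 9 + 14 + 22 = 79. Control: 14 + 20 + 22 + 13 + 21 = 90. The total of 169 equals the number of eligible participants in Recruitment. Without cohort 3 the arms are 79 − 9 = 70 and 90 − 22 = 68. Recruitment also says that 31 of the 169 left before starting, but not from which cohort or arm, so the weights below use all 169.

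**Bias if cohort is omitted.** Let D be the mean difference between cohort 3 and the rest. The intervention-minus-control contrast shifts by D × (9/79 − 22/90) = D × (0.114 − 0.244) = −0.131 D. If cohort 3 has the higher values, the shift favours the intervention.

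- HbA1c, D assumed 0.5 to 2.0 points: shift of 0.07 to 0.26 points.
- Fasting glucose, D assumed 10 to 40 mg/dl: shift of 1.3 to 5.2 mg/dl.

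The power calculation targets 1.0% HbA1c and 20 mg/dl.

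**Bias from a pure year difference.** Most documented changes separate year 1 from year 2, not cohort 3 from cohorts 4 and 5. Year 2 patients are (9 + 14 + 22)/79 = 45/79 = 57.0% of the intervention arm and (22 + 13 + 21)/90 = 56/90 = 62.2% of controls, a gap of 5.3 points. An assumed year difference of 1.0 HbA1c point would shift the contrast by about 0.05.

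**Effect of the selection rule.** The simulation used no treatment effect, the actual cohort-by-arm counts, residual SD of 1, and 20,000 runs (Monte Carlo standard error about 0.15 percentage points at 5%). The size of the cohort 3 shift is assumed. The article gives no retention threshold, so keeping cohort when a 4-df likelihood-ratio test has p < 0.05 is also an assumption.

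| Cohort 3 shift | Type I error, cohort omitted | Cohort always in | Cohort kept by likelihood ratio | How often kept | Bias left after selection |
|---|---|---|---|---|---|
| 0 | 5.1% | 5.0% | 5.1% | 6% | about 0 |
| 0.5 SD | 6.5% | 4.9% | 5.9% | 49% | 0.025 SD |
| 1 SD | 10.7% | 4.8% | 4.9% | 99% | about 0 |

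Retention by AIC gave 5.1%, 5.7% and 4.8%.

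**If every cohort had been balanced.** Omitting cohort would then make the test conservative: type I error of 3.7% and 1.6% with cohort means spread evenly over −0.5 to +0.5 SD and −1 to +1 SD. Cohort therefore belongs in the model even without the 9 vs 22 split.

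**Price of adjustment.** With a and b the arm sizes in each cohort, the stratified information is the sum of ab/(a + b): 6.74 + 10.24 + 6.39 + 6.74 + 10.74 = 40.86. Pooled it is 79 × 90/169 = 42.07. The ratio is 0.971, a loss of 2.9%.

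**The case against.** The best defence is that the harm is small. Cohort is already named as a candidate, and likelihood would normally keep it when its effect is large, which is where omission does most damage. The worst error rate in the table needs cohort to be dropped despite a 1 SD effect. Any use of the baseline value would shrink the bias further. Most primary endpoints are continuous, so the chi-square and Fisher point reaches mainly the medication percentage. All of this stands, and it limits the point to a should-fix.

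Four stronger readings are tempting, and the documents do not support them.

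- **That likelihood-based selection invalidates the nominal p-value.** The simulation gives about 5 to 6%, which is mild inflation.
- **That 9 of 31 shows faulty randomisation.** An exact binomial test against 1:1 gives p = 0.029, but it assumes 31 independent allocations, and the Randomization section says enrolled spouses were allocated in pairs. It also picks the most extreme of five cohorts: 1 − 0.971^5 is about 14%. The split needs an explanation; it proves nothing by itself.
- **That the article contradicts itself in saying** "The nature of the dietary and exercise intervention itself was not changed and did not vary across cohorts". That sentence concerns the nature of the diet and exercise. The sentence before it discloses the extra education and contact in weeks 4 and 6, and Table 1 shows the difference.
- **That a treatment-by-version interaction is needed.** Version coincides with year, so the interaction could not isolate it. Its standard error would also be about twice that of the main effect: √(2/34 + 1/45 + 1/56) = 0.31 against √(1/79 + 1/90) = 0.15, in SD units.

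**Conclusion.** The point holds in a limited form. The article randomises within cohort, reports one cohort at 9 vs 22 while describing the arms as roughly equal in each cohort, and then leaves cohort and baseline optional. Omitting cohort would shift the contrast by 0.131 times a difference specific to cohort 3, or about 0.05 times a pure year difference. Only the second kind of difference is well documented; apart from cohort 5 being the first programme run entirely by Marshallese staff, little separates cohort 3 from cohorts 4 and 5. The likely bias is therefore modest against a 1.0% HbA1c target.

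Selection by likelihood leaves less than that: 0.025 SD and 5.9% type I error at the least favourable of the three shifts tried. The shift sizes and the retention threshold are assumptions. The stronger reason to act is that the choice of primary model stays open after data collection in an unblinded trial, when closing it costs almost nothing.

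**What to change.** In Statistical Analyses:

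1. State that between-group models for continuous outcomes always include cohort (five levels) and the baseline value of the outcome. Exempt these two terms from the likelihood-based choice of covariates.
2. For binary outcomes such as the percentage taking diabetes medication, replace the unstratified chi-square and Fisher comparisons with a cohort-stratified Mantel-Haenszel analysis or a logistic model with cohort.
3. Add one sensitivity analysis without cohort 3 (70 vs 68).

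In Cohorts, explain how cohort 3 came to be 9 vs 22 and amend the statement that numbers were roughly equal in each cohort.

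The cost is about four degrees of freedom for cohort, about 3% of information and a change of wording. No new data are needed.
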